##### Triggers and flags for mental health patients

Mental health patients are typically excluded in AE studies, and specific methods for identifying AEs have not been published for this population. No trigger tool has been developed to identify AEs among admitted mental health patients, although the IHI has published a trigger tool for detecting adverse drug events (ADE) in the mental health setting.^35^ A Canadian review of patient safety in the mental health setting suggested eight domains that should be considered for mental health patients.^36^ We selected our flagged outcomes on telephone follow-up and triggers on medical record review based on these domains and the IHI mental health setting ADE trigger tool.^35^ We will include the following as additional flagged outcomes on telephone follow-up for patients whose index ED visit was for a mental health complaint: contact with mental health crisis lines, police, provincial child welfare agencies; attempted or actual self-harm; attempted or actual harm to others; attempted or actual harm by others. These flagged outcomes are in addition to those flagged outcomes outlined above on telephone follow-up. We will use the CPTT for admitted mental health patients, but will also consider the following to be triggers: any use of physical or chemical restraints, seclusion of the patient; any attempted harm to self, any attempted harm to or by others (including staff and other patients); any abscondment from the in-patient ward; and IHI mental health setting ADE triggers that are not also CPTT triggers.

##### Critically ill or deceased patients

It would be insensitive and unethical to approach families to participate in the study whose children die in the ED or who present with acute life-threatening injuries or illnesses that are not stabilised in the ED. Any children who die in the ED will be considered to have a flagged outcome and their medical record will be reviewed (stage 2 below) for an AE. Unstable children with life-threatening injuries or illnesses who were admitted to hospital will have their medical record screened by the research nurse using the CPTT. These children will be identified by the site research coordinator during his/her review of the ED registration list following each shift for ‘missed patients’ and entered into the study database.

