### Outcome measures

#### Primary outcome measure

The primary outcome will be the proportion of patients who experience an AE related to ED care within 3 weeks of an ED visit. We will use the Canadian Patient Safety Institute definition of an AE as an event that results in unintended harm to the patient, and is related to the healthcare and/or services provided to the patient rather than to the patient's underlying medical condition.^3^ Healthcare and services will be defined to include the actions of individual hospital staff as well the broader systems and care process.^6^
^7^ It will include harm related to acts of omission (failure to diagnose or treat) and commission (incorrect diagnosis or treatment, or poor performance).^6^ ED care will be defined as any care provided in the ED and will explicitly include care provided by ED specific staff (ie, staff physicians, nurses and allied healthcare providers) and care provided by consultants in the ED. Such a broad definition of ED care was chosen to reflect the overall patient experience and to be consistent with other studies.^12^
^13^ The time frame for primary outcome estimation (3 weeks) is based on research documenting that the majority of AEs for adult-related ED care happen within 72 h of the ED visit, that 85% occur within 2 weeks, and that the remainder occur within 3 weeks.^12^
^13^

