#### Data collection for patients admitted to hospital at the index ED visit

A trained research nurse will contact all admitted patients (and/or their parents) by telephone (or in person if currently admitted) at 7, 14 and 21 days following their visit to administer a structured interview and identify patients with flagged outcomes. The research nurse will also screen the medical record of all admitted patients using the Canadian Pediatric Trigger Tool (CPTT) to assess for the presence of triggers during the first 3 weeks of hospital admission. If telephone follow-up reveals the patient had an ED visit or admission to another hospital, we will attempt to obtain these records for review (having obtained consent to do so at enrolment).

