#### Data collection for enrolled patients ‘lost to follow-up’

For patients ‘lost to follow-up’, the research nurse will review the medical record for ED visits, outpatient visits, and admissions, and screen for triggers and flagged outcomes. The research nurse will also search, where permitted by provincial jurisdiction, the provincial coroner's database.

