##### Mental health patients

In order to not underestimate the risk of AEs among this vulnerable, high-risk population, we will take the following steps for children/youth with mental health complaints for whom it would not be appropriate to approach for consent (eg, critically ill children, such as children who are floridly psychotic or those who have presented with deliberate self-harm requiring resuscitation, and children who are behaviourally aggressive). For these children/youth, if they are admitted to hospital at their index ED visit we will complete at CPTT to look for ‘triggers’ in their record. For all children/youth in this group, we will also examine the electronic health record to determine whether the patient had a visit to the ED or admission in the 21 days following their index visit. If they are determined to have had a subsequent ED visit or admission, these patients will be considered to have flagged outcomes. Any patient with a flagged outcome or trigger will have their medical record will be reviewed (see stage 2 below) for an AE.

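### For unstable children who are admitted without a consent approach, no stated step looks for a return ED visit after ward discharge, although comparable groups get one

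*Protocol article*

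**What the plan says.** The primary outcome is "the proportion of patients who experience an AE related to ED care within 3 weeks of an ED visit" (Primary outcome measure). The same 3-week window applies to every patient.

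Under Critically ill or deceased patients, families of children who cannot be stabilised in the ED are not approached. The children are found during "review of the ED registration list following each shift for ‘missed patients’ and entered into the study database". For survivors the only stage 1 step given is: "Unstable children with life-threatening injuries or illnesses who were admitted to hospital will have their medical record screened by the research nurse using the CPTT".

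The section Mental health patients covers children with mental health complaints who cannot be approached, and names among them "critically ill children, such as children who are floridly psychotic or those who have presented with deliberate self-harm requiring resuscitation". Their inpatient step is the same: "if they are admitted to hospital at their index ED visit we will complete at CPTT to look for ‘triggers’ in their record". A second step applies to all of them, counted from the index visit: "we will also examine the electronic health record to determine whether the patient had a visit to the ED or admission in the 21 days". Any such visit is a flagged outcome.

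For enrolled children who cannot be reached, "the research nurse will review the medical record for ED visits, outpatient visits, and admissions, and screen for triggers and flagged outcomes". Consented admitted children are contacted at days 7, 14 and 21 as well as being screened with the Canadian Pediatric Trigger Tool (CPTT).

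The CPTT window is worded in two ways. The data collection section for admitted patients has the nurse use the tool "to assess for the presence of triggers during the first 3 weeks of hospital admission". The section on triggers among admitted patients counts 3 weeks from the index ED visit.

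**The concern.** Telephone follow-up depends on consent, so unstable children who are never approached have no interview. Their AE search rests on a tool for admitted patients, while their outcome window runs to day 21 whether or not they are still in hospital. If such a child goes home, returns to the ED and is sent home again, no stated stage 1 step picks up that visit unless another trigger has already been found. A child resuscitated after deliberate self-harm, whose family likewise was not approached, would have the same visit flagged.

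At stake is a one-sided loss of events in children whom the protocol itself describes as possibly at particular risk. It would affect the medical/surgical and high-acuity estimates listed under Subgroup analyses, but not the mental health estimate. It also cannot be repaired at analysis if the record was never searched.

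**Working it through.** **Stated search for later visits, by group**

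| Group | CPTT if admitted | Stated search for visits after discharge |
|---|---|---|
| Consented, admitted | yes | contact at days 7, 14 and 21 |
| Enrolled, lost to follow-up | screened for triggers | ED visits, outpatient visits, admissions |
| Mental health, not approached | yes | ED visit or admission within 21 days |
| Unstable, not approached, admitted | yes | none stated |

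Of the groups given a search method, the last is the only one whose members survive the ED visit and have no stated search for later visits. Unplanned admission is a listed CPTT trigger. With the window counted from the index visit, a readmission to the same hospital may therefore be caught. What remains is a return ED visit without admission in a child with no other trigger.

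**The plan's own precision figure**

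Inputs from Sample size: p = 0.05, d = 0.006, 95% confidence, 10% loss to follow-up.

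n = z²p(1−p)/d² = 1.96² × 0.05 × 0.95 / 0.006² ≈ 5069. Then 5069/0.9 = 5632.2, against 5632 stated, and 5069 × 0.05 ≈ 253 expected AEs. The plan's figures reproduce, and nothing here changes them. The margin to compare with is 0.6 points.

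**Size of the gap**

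None of these inputs is in the documents; all are assumptions:
- share of the cohort in this group: 0.5% (range 0.2% to 1%);
- return after ward discharge: 10% (range 5% to 20%);
- share of returns that reflect an ED-care AE: 20% to 50%;
- high-acuity subgroup: 10% of the cohort, 5632 × 0.10 ≈ 563.

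Missed patients = 5632 × group share × return share × AE share.
- Group size: 5632 × 0.005 ≈ 28 (11 to 56).
- Central: 28 × 0.10 × (0.2 to 0.5) ≈ 0.6 to 1.4 patients.
- Extremes: 11 × 0.05 × 0.2 ≈ 0.1; 56 × 0.20 × 0.5 ≈ 5.6.

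Shift in the overall proportion (divide by 5632): 0.01 to 0.025 points, at most 0.1. Relative to the margin: 0.01/0.6 ≈ 2% to 0.025/0.6 ≈ 4%, at most 0.1/0.6 ≈ 17%.

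Shift in the high-acuity subgroup (divide by 563): 0.1 to 0.25 points; all extremes together give 1.0. The sampling half-width there at 5% is 1.96 × √(0.05 × 0.95/563) ≈ 1.8 points, before any design effect.

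For the given inputs these are upper bounds. They treat every AE-related return as missed, including readmissions, returns in children already flagged by another trigger, and returns in children already counted with an ED-care AE.

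**The case against.** Several counter-arguments stand and limit the point.

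- **The search does not plainly stop at discharge.** A reader might infer that it does. The trigger section counts 3 weeks from the index visit, and it is the child's medical record that is screened.
- **Most triggers are not shown.** The article names eight examples of 35 and says the list is not complete. It cannot be said that no trigger would respond to a return ED visit, only that no stated step looks for one.
- **One trigger is enough.** These are very ill children, and listed triggers include arrest, any infection and transfer to higher-level care. Once triggered, a child gets a case summary that covers return visits, and reviewers can see later ED records (Preparation of case summaries).
- **Length of stay over 21 days does not measure coverage.** A reader might infer that a 3-day stay covers only a seventh of the risk. Primary outcome measure reports, for adult ED care, that most AEs fall within 72 hours and 85% within 2 weeks.
- **The groups are not fully parallel.** No trigger tool exists for admitted mental health patients, and their look-up also serves children who were never admitted. That explains part of the difference, but not the critically ill, admitted mental health child.
- **Denominator membership is implied, not stated.** The children are entered in the database, while Ethical considerations says nobody is enrolled without written consent. If they are left out of the denominator, this bias does not arise.

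That the article is condensed is a weaker defence. It spells out the procedure for both groups in neighbouring sections, and the procedures differ with no reason given there.

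**Conclusion.** The gap holds in a narrow form: a return ED visit without admission, after ward discharge, in an unstable child who was not approached and has no other trigger. If these children are in the denominator, the bias runs only towards fewer AEs.

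Under the assumed inputs it is negligible for the primary proportion and small for the high-acuity subgroup, well inside sampling error in both at the central values. A reader might infer material harm to a critically ill estimate. The documents do not support that: no such estimate is planned, and the listed high-acuity group also contains emergent patients and stabilised resuscitation patients, who are approached for consent.

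The main consequence is that medical/surgical and mental health children are searched to different depths over the same 3 weeks. This is a minor improvement worth making because it is cheap and cannot be made later from data never collected.

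**What to change.** In Critically ill or deceased patients, add the look-up already set for mental health children who are not approached: the electronic health record is examined for any ED visit or admission in the 21 days after the index visit, and any such visit is a flagged outcome that goes to stage 2. State also that the CPTT screen for this group runs to day 21 from the index visit and includes readmissions, as the trigger section already words it.

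The cost is a sentence or two of protocol text and a short extra look-up for probably a few dozen children (assumed), by the same research nurse. Ethics boards may need notice that record review without consent runs to day 21 for this group, as it already does for the mental health group.

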##### Mental health patients

In order to not underestimate the risk of AEs among this vulnerable, high-risk population, we will take the following steps for children/youth with mental health complaints for whom it would not be appropriate to approach for consent (eg, critically ill children, such as children who are floridly psychotic or those who have presented with deliberate self-harm requiring resuscitation, and children who are behaviourally aggressive). For these children/youth, if they are admitted to hospital at their index ED visit we will complete at CPTT to look for ‘triggers’ in their record. For all children/youth in this group, we will also examine the electronic health record to determine whether the patient had a visit to the ED or admission in the 21 days following their index visit. If they are determined to have had a subsequent ED visit or admission, these patients will be considered to have flagged outcomes. Any patient with a flagged outcome or trigger will have their medical record will be reviewed (see stage 2 below) for an AE.

##### Preparation of case summaries

Any patient deemed to have a flagged outcome on telephone follow-up or a trigger on medical record review will have a case summary prepared by a research nurse. We will orient each site's research nurse on case summary creation. The case summaries are intended as narrative descriptions of what occurred at the index ED visit and the outcome. This technique is used in order to reduce the risk of handwriting recognition by examining the health record itself. These summaries will include: (1) patient demographics; (2) index ED visit details (such as date of visit, presenting complaint, vital signs, history of presenting illness, physical examination, investigations, treatment, etc.); (3) flagged outcome/trigger details (such as description of symptoms, date of return visits, ED visit details, and discharge or death summary details). Copies of the index ED visit, subsequent ED visits, discharge summary or death summary, as well as laboratory and other investigations (such as ECG and chest X-ray reports) will be accessible to the physician reviewers as required and will be de-identified.

#### Stage 2: identification of AEs

After standardised, comprehensive training, three ED physicians will independently review the case summary of each patient. They will then complete a computerised structured outcome assessment form. These reviewers will be blinded to patient name and sex, date and time of visit, treating physician, and study site. If the reviewers are unable to make their AE determinations based on the narrative case summary alone, they will have access to the key components of the medical record used in creating the case summary (blinded as outlined above). The reviewers will then be asked to independently determine whether the flagged outcome or trigger may be associated with healthcare management and rate their certainty of this determination on a six-point Likert scale used in previous studies (see online supplementary appendix 1).^4^
^6^
^7^
^12^
^13^
^29^ On this six-point Likert scale, 1 represents a flagged outcome or trigger was most certainly due to disease and 6 represents that it was most certainly due to care. If two reviewers have a level of certainty ≥4, the outcome will be classified as an AE. If one reviewer reports a level of certainty ≥5, while the remaining report <4, the reviewers will discuss the case and reconsider their scoring. We have chosen to use three physician reviewers as previous research has shown that combining multiple reviews reduces uncertainty over the presence of an AE.^37^ To ensure that local practice patterns are considered during the review, the reviewer panel will include two site-specific reviewers and one reviewer from the coordinating site. One reviewer will determine whether the AEs were preventable using a four-point Likert scale with AEs classified as preventable if the reviewer has a certainty ≥3 (see online supplementary appendix 1) and can clearly identify the factor or factors that made the AE preventable. A single reviewer will also classify the AE type(s), severity and system response required. Previous work has shown that a single reviewer is adequate for this step.^37^

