##### Identification of AE's in patients with mental health entrance complaints

These cases will be reviewed by 2 ED physicians and a psychiatrist (rather than only ED physicians). The same methodology as outlined above will be used to determine if the patient suffered an AE.

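### Two of the three outcome reviewers are seated because they belong to the treating site, so the stated blinding to study site cannot hold for them

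*Protocol article*

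**What the plan says.** All of the key text is in the protocol article, section *Stage 2: identification of AEs*.

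- Number and independence: "three ED physicians will independently review the case summary of each patient".
- Blinding: "These reviewers will be blinded to patient name and sex, date and time of visit, treating physician, and study site".
- Panel: "the reviewer panel will include two site-specific reviewers and one reviewer from the coordinating site". The reason given is "To ensure that local practice patterns are considered during the review".
- Decision rule, on a six-point certainty scale: "If two reviewers have a level of certainty ≥4, the outcome will be classified as an AE".
- The only further step: "If one reviewer reports a level of certainty ≥5, while the remaining report <4, the reviewers will discuss the case and reconsider their scoring".

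Two neighbouring sections also bear on the point. *Preparation of case summaries* explains that nurses write narratives so that handwriting is not recognised, and lists among the contents "index ED visit details (such as date of visit, presenting complaint, vital signs, history of presenting illness". The section on mental health complaints changes the panel: "These cases will be reviewed by 2 ED physicians and a psychiatrist (rather than only ED physicians". It does not say whether the psychiatrist takes a local seat or the coordinating-site seat.

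**The concern.** The primary outcome is the proportion of children with an AE related to ED care. For every flagged case it depends on a graded judgement of whether disease or care was the cause. Blinding to site and to treating physician is what the article offers as protection for that judgement.

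A reviewer chosen because the case is from their own hospital, in order to apply that hospital's practice, knows the site. The blinding statement therefore describes a property that the design does not have for two of the three reviewers. Blinding to treating physician also protects less against a colleague in the same department than against an outsider, who would not recognise the staff or the case. The article states no rule that keeps a physician who treated the child off that child's panel.

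Readers of the results would take the AE proportion to come from site-blinded assessors. In fact, physicians of the department under assessment hold most of the votes.

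**Working it through.** **1. The two statements side by side.** The blinding sentence covers the reviewers as a group and includes study site. The panel sentence contrasts site-specific reviewers with one from the coordinating site, and the stated aim is to bring in local practice. That aim is met only if the site-specific reviewers come from the site that treated the child. Both statements cannot be true of those two reviewers.

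**2. What the voting rule does.** Call a score of 4 or more a yes. There are 2 × 2 × 2 = 8 vote patterns.

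| Two local reviewers | Coordinating-site reviewer | Result |
|---|---|---|
| both yes | any score | AE; no discussion |
| both no | below 4 | not an AE |
| both no | exactly 4 | not an AE; no discussion |
| both no | 5 or 6 | discussion; becomes an AE only if a local reviewer re-scores to 4 or more |
| one yes, one no | 4 or more | AE |
| one yes, one no | below 4 | not an AE, unless the local yes was 5 or 6, which prompts discussion |

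The fourth row assumes that the two-of-three rule is applied again after re-scoring. In the 4 of 8 patterns where the local pair agree, their vote is the initial result. In the 4 where they split, the coordinating-site reviewer's vote gives the initial result. Discussion is prompted only by a lone high score, so an outside reviewer who disagrees with two local yes votes has no route to discussion.

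**3. The plan's own yardstick.** Inputs from *Sample size*: proportion 5%, margin 0.6 points, 95% confidence, 10% loss to follow-up.

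- n = 1.96² × 0.05 × 0.95 / 0.006² = 5068.6, so 5069, as the article states.
- 5069 / 0.9 gives 5633 rounded up, against the stated 5632, so the figure is reproduced.

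The sample size does not depend on this point. The 0.6-point margin only gives a scale for step 4.

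**4. Illustration on assumed inputs.** The documents give no reviewer sensitivity. Let a local reviewer score a true AE as yes with probability l and the coordinating-site reviewer with probability c, independently, with no false positives and no discussion step.

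- Detection by the panel = l² + 2l(1 − l)c.
- No local difference, l = c = 0.8: 0.64 + 0.32 × 0.8 = 0.896.
- Local reviewers lower, l = 0.7, c = 0.8: 0.49 + 0.42 × 0.8 = 0.826. A 5.0% proportion becomes 5 × 0.826 / 0.896 = 4.61%, a shift of −0.39 points.
- Local reviewers higher, l = 0.9, c = 0.8: 0.81 + 0.18 × 0.8 = 0.954. The 5.0% becomes 5 × 0.954 / 0.896 = 5.32%, a shift of +0.32 points.
- Range with c from 0.7 to 0.9 and local reviewers 0.1 to 0.2 lower. Lowest (c = 0.7, l = 0.5): 5 × 0.600 / 0.784 = 3.83%. Highest (c = 0.9, l = 0.8): 5 × 0.928 / 0.972 = 4.77%.

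The sign follows entirely from the assumption about l, and with l = c the shift is zero.

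**The case against.** Two local reviewers and one central reviewer is a deliberate choice with a stated reason. Physicians who know local protocols may see departures from them that an outsider would miss. Reviewers are also blinded to patient name, sex, date and time, and treating physician. Narratives replace handwritten notes, and record copies are de-identified. About 5632 of roughly 470 000 annual visits are enrolled (1.2%), and only flagged cases reach review, so recognising a particular case is possible but not likely. Knowing the site is not knowing the physician. Reviewers are trained, and interobserver reliability is checked on 5% of records.

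Most of this stands, and it rules out several stronger conclusions that a reader might infer.

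- *That the treating department's physicians always decide the primary outcome.* They do not. When the local pair split, the coordinating-site reviewer's vote counts, and a lone score of 5 or more prompts discussion. Mental health panels differ again.
- *That the AE proportion is biased downward by a known amount.* Nothing in the documents fixes the direction or the size.
- *That site differences and reviewer differences cannot be separated.* A coordinating-site reviewer scores cases from every site independently, which gives a partial common reference. Comparing sites is also not a stated objective.
- *That the coordinating site's own cases are reviewed entirely in-house.* The article does not say which site coordinates or whether it is one of the nine.
- *That the panel must be rebuilt with an outside majority.* That trades local knowledge for independence, and the documents do not show which is better.

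The objection does not remove the contradiction about site blinding. Protection against recognising the physician is also partial: the visit date appears both among the blinded items and among the summary contents. Agreement statistics would not reveal leniency or strictness that two local reviewers share.

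**Conclusion.** The site-blinding claim is wrong as written for two of the three reviewers. This rests on reading site-specific as belonging to the treating site, which the stated purpose supports. Blinding to treating physician is weaker for those two than for an outsider, and the article states no rule that excludes a treating clinician. The local pair's vote stands whenever they agree, apart from the narrow discussion route.

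The effect on the AE proportion is unknown. Under assumed differences of 0.1 in scoring probability it could be a few tenths of a point either way, which is not negligible beside a 0.6-point margin, and a larger sample would not remove it. With no scoring difference there is no effect. The plan already provides for independent scores from both kinds of reviewer, so the question can be answered from the study's own data.

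**What to change.** 1. Limit the site-blinding statement to reviewers who are not from the treating site. Say plainly that local reviewers know the site. Reconcile the visit date between the blinding list and the summary contents.
2. State that no physician involved in the child's care reviews that case. If a review manual already says so, state it in the protocol as well.
3. Keep each reviewer's score from before any discussion. Report, by site, the agreement and the share of cases scored 4 or more for local versus coordinating-site reviewers. Say which seat the psychiatrist takes on mental health panels. If the coordinating site is one of the nine, show its own cases separately, because there the third reviewer is not an outsider.
4. Add a sensitivity analysis of the primary proportion that classifies cases on the coordinating-site reviewer's initial score alone. Read it together with item 3, because one reader and a majority of three detect differently even without local leniency. If every reviewer has probability 0.8, a single reader gives 0.8 and the panel 0.896, so 5.0% becomes 5 × 0.8 / 0.896 = 4.46%.

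The cost is a little more analysis and a check at case assignment. No extra reviews or patients are needed. Replacing one local reviewer with one from another participating site is open to the investigators as an option. It would mean sending summaries, and sometimes record copies, to further hospitals, and it is not a required correction.
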